# Training dual-task walking in community-dwelling adults within 1 year of stroke: a protocol for a single-blind randomized controlled trial

**DOI:** 10.1186/1471-2377-12-129

**Published:** 2012-10-31

**Keywords:** Stroke, Gait, Dual-task, Attention, Cognition, Rehabilitation, Obstacle avoidance, Participation, Physical therapy

## Abstract

**Background:**

Community ambulation is a highly complex skill requiring the ability to adapt to increased environmental complexity and perform multiple tasks simultaneously. After stroke, individuals demonstrate a diminished ability to perform dual-tasks. Current evidence suggests that conventional rehabilitation does not adequately address gait-related dual-task impairments after stroke, which may be contributing to low levels of participation and physical inactivity in community-dwelling stroke survivors. The objective of this study is to investigate the efficacy of dual-task gait training in community-dwelling adults within 1 year of stroke. Specifically, we will compare the effects of dual-task gait training and single-task gait training on cognitive-motor interference during walking at preferred speed and at fastest comfortable speed (Aim 1), locomotor control during obstacle negotiation (Aim 2), and spontaneous physical activity (Aim 3).

**Methods/Design:**

This single-blind randomized controlled trial will involve 44 individuals within 12 months of stroke. Following baseline evaluation, participants will be randomly allocated to single- or dual-task gait training. Both groups will receive 12, 30-minute sessions provided one-on-one over 4–6 weeks in an outpatient therapy setting. Single-task gait training involves practice of gait activities incorporating motor relearning principles. Dual-task gait training involves an identical gait training protocol; the critical difference being that the dual-task gait training group will practice the gait activities while simultaneously performing a cognitive task for 75% of the repetitions. Blinded assessors will measure outcomes at baseline, post-intervention, and 6 months after completion of the intervention. The primary outcome measure will be dual-task effects on gait speed and cognition during unobstructed walking. Secondary outcomes include spatiotemporal and kinetic gait parameters during unobstructed single- and dual-task walking at preferred and fastest comfortable walking speeds, gait parameters during high and low obstacle crossing, spontaneous physical activity, executive function, lower extremity motor function, Timed Up and Go, balance self-efficacy, number of falls, and stroke-related disability. Hypotheses for each aim will be tested using an intention-to-treat analysis with repeated measures ANOVA design.

**Discussion:**

This trial will provide evidence to help clinicians make decisions about the types of activities to include in rehabilitation to improve dual-task walking after stroke.

**Trial registration:**

ClinicalTrials.gov NCT01568957

## Background

The achievement of community ambulation after stroke is critical for active participation in everyday activities, preventing social isolation and depression, and enhancing quality of life
[1,2]. In the period following discharge, many stroke survivors report low levels of participation in activities outside the home, with walking ability being a major factor influencing community reintegration
[3]. Functional community ambulation requires an ability to perform cognitive tasks while walking, and an ability to adapt to extrinsic environmental factors that increase the complexity of mobility, such as obstacle avoidance (e.g., curbs) and time-critical tasks (e.g., crossing the street within the time constraints imposed by traffic signals)
[4]. A reduced capacity for dual-task walking and/or limited ability to adapt to changes in environmental context may substantially restrict the degree to which a person is able to participate in his/her life roles.

After stroke, performance of a cognitive task concurrently with walking results in a profound reduction in gait speed
[5-7], with corresponding effects on stride duration
[5,8,9], stride length
[5,6], double limb support time
[7,10], and cadence
[5,11] (referred to as *dual-task interference,* or *cognitive-motor interference*). Diminished capacity to walk with adequate speed while performing a cognitive task may increase disability in the community or lead to curtailing of participation in everyday activities. Although dual-task performance can also affect the cognitive task
[6,11], most research indicates that patients with stroke prioritize the cognitive task, sacrificing gait performance
[5,6,8,9].

Current evidence suggests that conventional rehabilitation does not adequately address gait-related dual-task impairments after stroke. Although Cockburn and colleagues
[9] found that 7 out of 10 patients showed a reduction in dual-task cost on stride duration after customary rehabilitation, most patients continued to exhibit considerable dual-task interference during walking at discharge, as well as simultaneous interference in the cognitive task. Specific training in dual-tasking may be necessary to improve dual-task walking in people with stroke. A reduction in dual-task interference may be achieved via at least two possible mechanisms: (1) improving automatization of walking by repetitive practice; gait automaticity reduces the attentional requirements of gait, thereby increasing the capacity to perform simultaneous cognitive tasks; and (2) improving dual-task coordination by task-specific training; targeted practice of gait-related dual-tasks may improve performance in these activities. Theoretically, DTGT should result in greater improvement in dual-task performance (reduced dual-task cost) than STGT; however, both may act to increase gait automatization
[12,13], since both approaches involve repetitive practice of walking. There is mounting evidence of the value of task-specific training in neurological rehabilitation
[14,15]. This evidence indicates that practice should be task-specific and relevant to the patient and context. Based on the principles of task-specific training, practice of dual-task activities during locomotion in a variety of environmental contexts is needed to improve dual-task performance.

Although dual-task training in older adults has been shown to have promise
[13,16], there has been little research on dual-task training in stroke. In a randomized controlled trial, Yang et al.
[17] compared a motor-motor dual-task intervention (walking while manipulating either one or two balls of various size) to a no-intervention control. Compared to 12 patients who did not receive any intervention, the 13 patients who received dual-task training significantly improved their gait speed during both single-task and dual-task (tray carrying) walking. Our pilot data
[18] provide preliminary evidence that a cognitive-motor dual-task intervention can reduce dual-task interference in gait and increase community participation in community-dwelling stroke survivors. However, due to absence of a control intervention in either study, it is not possible to know whether improvements were due to repetitive walking practice (i.e., gait automatization) or the inclusion of dual-task activities (i.e., task-specific training in dual-task coordination). Research is needed to directly compare dual-task gait training to more traditional, single-task gait training approaches in order to identify the optimal parameters of gait rehabilitation that can improve walking and reduce dual-task interference after stroke.

The primary aim of this study is to investigate the effects of dual-task gait training (DTGT) compared to single-task gait training (STGT) on dual-task interference in community-dwelling adults within one year of stroke. Our hypothesis is that DTGT mediates the coordination of dual-tasks and will reduce cognitive-motor interference more than STGT. By measuring dual-task effects in both gait and cognitive tasks, we will be able to examine whether the intervention affects the voluntary allocation of attentional resources during dual-task walking. The second aim is to investigate the effect of DTGT on a more ecologically valid attention-demanding task: obstacle avoidance. Although obstacle crossing has been studied in people with stroke
[19-23], there have not been any studies investigating whether training in attentionally-demanding tasks can improve locomotor control during obstacle avoidance. The third aim is to examine the effect of the intervention on participation by quantitatively measuring ambulation and physical activity in the participants’ natural environment using innovative, wireless sensor technology. Despite the considerable threat to participation in everyday life posed by diminished dual-task capacity, research has not previously investigated the relationship between dual-task interference and community participation. This study addresses this important question, and will determine whether DTGT increases community participation more than STGT. Knowing whether an intervention has resulted in meaningful change in a person’s ability to participate in the real world is the ultimate indicator of therapeutic effectiveness.

## Methods

### Design

This study is a single-blind randomized controlled trial of DTGT versus STGT in an outpatient therapy setting. Following baseline assessment, participants will be randomly assigned to one of the two intervention groups. The primary outcome is dual-task effect on gait speed and cognition (reaction time and accuracy) during unobstructed walking at preferred and fastest comfortable walking speeds. We include the fastest comfortable speed condition to investigate the effects on the intervention on a more attention-demanding gait task. The flow of the trial is illustrated in Figure
1.

**Figure 1 F1:**
[figure not shown]
Flow of trial.

### Participants

The participants will be 44 community-dwelling adults within 12 months of stroke. To be included in the study participants must satisfy the following criteria: (a) ≥ 18 years, (b) a diagnosis of stroke consistent with the World Health Organization definition
[24] and, where possible, confirmed by CT or MRI, (c) be within 12 months of stroke onset, (d) living in the community, defined as living in one’s home or the home of a friend, relative, or caregiver, (e) able to walk without assistance of another person, (f) self-selected gait speed 0.6 -1.1m/s determined during a 10m walk test, (g) score > 23 on the Montreal Cognitive Assessment (MoCA)
[25], which is the cut off at which the sensitivity and specificity of the MoCA are optimized
[26]. All participants must be medically stable and approved for participation by the study physician. Additionally, patients must have been discharged from conventional outpatient physical therapy before commencing study interventions. Thus, the patients will be receiving only the study-related physical therapy. Exclusion criteria for the study include: (a) neurological conditions other than stroke, (b) any orthopedic or cardiopulmonary problems limiting gait or physical activity, (c) previous stroke with residual motor deficit, (d) inability to follow a 3-step command, (e) uncontrolled hearing impairment, (f) severe uncontrolled visual impairment, (g) speech-language impairment affecting ability to respond verbally to auditory stimuli, determined by speech-language pathologist, (h) Timed Up and Go test > 15 seconds, (i) lower extremity amputation, (j) not living in the community prior to stroke, and (k) concurrent participation in another clinical trial.

### Randomization and blinding

Following baseline evaluation, the participants will be randomized to either DTGT or STGT using a 1:1 randomization sequence prepared by the study biostatistician. Group assignment will be concealed using opaque envelopes, which will be opened after the completion of the baseline assessment. Research personnel conducting the baseline, post-intervention, and follow-up assessments will be blind to group assignment. The investigator processing the data extracted from activity monitoring will also be blind to group assignment. Participants will be aware of their group allocation, but will be naïve to the study hypotheses. Therapists providing the study interventions cannot be blinded in this study design.

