To measure spontaneous physical activity, participants will wear a physical activity monitor (PAMSys™, Biosensics LLC, MA, USA) embedded in a lightweight breathable T-shirt worn under clothing for two consecutive days after each evaluation. This device uses a combination of miniaturized kinematic sensors housed in a single portable sensor attached to the chest. It can detect body posture (e.g., sitting, lying) as well as provide an accurate assessment of periods of locomotion (e.g., walking, turning), including gait inter-cycle variability during activities of daily living. The validity of this approach has been established in three separate pilot studies and by benchmarking the results with independent analysis by an optical motion system
[33-35].

Executive function will be assessed using a computerized Stroop test
[36]. DirectRT (Empirisoft, New York, NY) software will record the participants’ reaction times and responses. We will use color-word interference accuracy scores and reaction times to assess executive function at each assessment. Lower extremity motor function will be assessed using the Fugl-Meyer Motor Assessment scale
[37]. Functional gait performance will be evaluated using the Timed Up and Go test
[38], and the Activities-specific Balance Confidence Scale
[39] will measure balance self-efficacy. The Stroke Impact Scale
[40] will be used to assess stroke-specific disability. Participants will keep a falls diary between the post-intervention assessment and the 6-month follow-up assessment. Any participant reporting a fall will receive a phone call from the research team to obtain information about the fall and any related injuries.

Additional measures conducted at baseline to further characterize the study sample include: Digit Symbol Modalities Test (speed of processing)
[41], Comprehensive Trail Making Test (inhibition of distraction)
[42], and the Star Cancellation Test (unilateral spatial neglect)
[43], National Institutes of Health Stroke Scale (stroke severity)
[44], 6-minute walk test (walking endurance)
[45], Melbourne Edge Test (contrast sensitivity), and lower extremity sensation and proprioception. Demographic data including age, time since stroke, medical history, employment status and living situation will also be collected at baseline.

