#### Data analysis plan

DTGT and STGT groups will be compared on baseline characteristics using Student *t*-tests for continuous data and Fisher’s exact test for proportions. The hypotheses will be tested using an intention-to-treat analysis, applying a repeated measures design whereby the two groups will be compared on primary outcomes at: (i) baseline, (ii) after the completion of the intervention, and (iii) 6 months following completion of the intervention. For the primary outcomes of dual-task effects on gait and cognition, a 2 x 3 mixed model repeated measures ANOVA with group (DTGT, STGT) as between-subjects factor and time (pre-training, post-training, 6-month follow-up) as within-subjects factor will be applied to DTE for each gait task separately (preferred walking, fast walking) and for each cognitive task separately (Stroop, clock). A similar analysis will be performed for all secondary outcome measures. Tukey’s honestly significant difference (HSD) post-hoc tests will be applied to examine the significant differences for all ANOVAs. If the normality assumptions for ANOVA are not supported, nonparametric equivalent statistical methods including Mann–Whitney *U*-tests and Wilcoxon signed-ranks tests will be used.

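### The stated primary model makes no use of time since stroke, although entry spans the first 12 months and the variable is collected: a cheap, low-priority gain in precision

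*Protocol article*

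**What the plan says.** All references are to the protocol article.

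- **Entry (Participants).** "The participants will be 44 community-dwelling adults within 12 months of stroke". The time criterion is "be within 12 months of stroke onset", with no minimum. Other criteria restrict who can enter early: "patients must have been discharged from conventional outpatient physical therapy before commencing study interventions", and "self-selected gait speed 0.6 -1.1m/s determined during a 10m walk test". Community living, walking without another person's help, MoCA above 23 and a Timed Up and Go of no more than 15 seconds are also required.
- **Allocation (Randomization and blinding).** "the participants will be randomized to either DTGT or STGT using a 1:1 randomization sequence prepared by the study biostatistician". The article does not say whether the sequence has strata or blocks.
- **Baseline data (Secondary outcome measures).** "Demographic data including age, time since stroke, medical history, employment status and living situation will also be collected at baseline".
- **Primary analysis (Data analysis plan).** The model has "group (DTGT, STGT) as between-subjects factor and time (pre-training, post-training, 6-month follow-up) as within-subjects factor". It is applied to DTE separately for each gait task and each cognitive task. Time in this model means the assessment visit, not time since stroke. The arms are compared on baseline characteristics by significance tests, but no adjustment is tied to the result.

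**The concern.** The trial asks which training lowers dual-task interference more, between baseline and a visit 6 months after a programme of 4 to 6 weeks. Someone enrolled soon after stroke and someone enrolled near month 12 are observed over different parts of recovery. If DTE changes at a different rate in these two kinds of patient, two things follow under the stated model. The difference in rates is counted as residual variation. And if one arm happens to receive more early patients, the estimate is not corrected for it, even though the variable needed is in the data set. With 44 patients, any avoidable residual variation is worth removing.

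**Working it through.** **1. Which variation is affected.** DTE is a percentage of single-task performance at the same visit, so recovery that improves single-task and dual-task performance in proportion cancels. The model contains the baseline visit, so a stable difference in DTE between early and late patients drops out of the group-by-visit comparison. What remains is a difference in the rate of change of DTE by time since stroke. For the same reason, a main effect of time since stroke alone would do almost nothing for the group-by-visit test. Its interaction with visit does the work.

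**2. Reproducing the plan's figure.** Inputs from Sample size calculation: difference 10 points, within-group SD 10.15, power 80%, alpha 0.05. Sidedness is not stated; two-sided fits.

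- Standardized difference = 10 / 10.15 = 0.985.
- A two-sided two-sample t-test needs 17.19, so 18 per group, which matches the article.
- Standard error at 18 per arm = 10.15 × √(2/18) = 3.38 points. Noncentrality = 10 / 3.38 = 2.96. With 34 degrees of freedom, power = 81.9%.

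**3. If 10.15 already includes the variation due to time since stroke.** Adjustment reduces the SD to 10.15 × √(1 − R²), where R² is the share of variance that the covariate explains. The documents give no R²; 0.05 to 0.20 is an assumption.

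| Assumed R² | Residual SD | Power, 18 per arm |
|---|---|---|
| 0 (unadjusted) | 10.15 | 81.9% |
| 0.05 | 9.89 | 83.8% |
| 0.10 | 9.63 | 85.7% |
| 0.20 | 9.08 | 89.4% |

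**4. If 10.15 does not include it.** The SD in the unadjusted analysis is then 10.15 / √(1 − R²).

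| Assumed R² | Unadjusted SD | Power, 18 per arm |
|---|---|---|
| 0.05 | 10.41 | 79.9% |
| 0.10 | 10.70 | 77.8% |
| 0.20 | 11.35 | 72.9% |

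Here adjustment would bring the SD back to 10.15 and power back to about 82%.

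**5. Price of the covariate.** With 36 evaluable patients, the between-patient residual degrees of freedom fall from 34 to 33, and the within-patient ones from (36 − 2) × 2 = 68 to 66. If the covariate explained nothing, power in the simple comparison would move from 81.9% to 81.8% (same noncentrality, 33 degrees of freedom).

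**Limits of the check.** It treats the primary question as one two-group comparison, as the article's own sample size does, and not as the full 2 × 3 model. The article gives no source for 10.15 and does not say whether it is the SD of DTE at one visit or of a change, so steps 3 and 4 cannot be narrowed to one case.

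**The case against.** The case against is substantial, and most of it stands.

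- **The sequence.** A reader might infer that allocation is unstratified. The article does not say so. It names no strata or blocks, but a condensed article commonly leaves these details to the full protocol, so its silence is not a finding.
- **Bias.** A reader might infer that an uneven share of early patients biases the result. Randomization leaves the comparison unbiased over repeated trials, and the standard error already allows for chance imbalance in any prognostic factor. What is lost is precision, together with the chance to correct an imbalance in the one trial that is run.
- **Spontaneous recovery.** A reader might take the Background's report that 7 of 10 patients reduced their dual-task cost on stride duration as evidence of natural recovery. It describes change after customary rehabilitation, on a gait measure other than gait speed, and does not relate the change to time since stroke. Nothing in the article shows that time since stroke predicts change in DTE.
- **The entry window.** The functional criteria and the required discharge from outpatient therapy will keep out many very early patients. They narrow the window but set no lower time limit.
- **Covariates left to the SAP.** Further covariates may be listed in an analysis plan that is not shown. Against this, the article states its primary model in some detail, "a 2 x 3 mixed model repeated measures ANOVA with group (DTGT, STGT) as between-subjects factor" with visit as the other factor. The suggestion is a change to that stated method.

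What survives is that a plausible prognostic variable is collected and is absent from the stated model.

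**Conclusion.** The point holds as an efficiency suggestion. The stated primary model omits time since stroke although entry spans up to 12 months and the variable is recorded. The analysis remains valid without it, and no passage contradicts another.

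The size of the gain is unknown. For an assumed R² of 0.05 to 0.20, power at 18 per arm rises from about 82% to about 84-89% if 10.15 already contains this variation. Otherwise unadjusted power is about 80% to 73%, against a planned 80%. If time since stroke hardly predicts change in DTE, nothing is gained and almost nothing is lost.

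The documents do not support a statement that the arms will be unbalanced, or a figure in DTE points for the effect of such an imbalance. That would require the share of early patients and their extra improvement, and neither is given. Priority: low; a cheap improvement.

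**What to change.** In Data analysis plan, pre-specify time since stroke at baseline, as a continuous variable, together with its interaction with visit, as a covariate in the primary DTE models. Do this before outcome data are seen by arm, and include the covariate whatever the baseline significance tests show.

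Cost: one sentence in the plan, no new data or patients, and one or two degrees of freedom in each part of the model. A linear term may fit poorly if change levels off with time since stroke, and the gain is small if the covariate is weakly prognostic.
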